#### Data analysis

Our research officer will collate data from all health centres on a monthly basis and feed them into a database created via SPSS kept on a mobile computer. There will be an assessment of smoking status by intervention category, analysed on an intention to treat basis. The point abstinence will be compared between the intervention and control arms at 4 weeks after the completion of the treatment and in controls 4 weeks after they were given the leaflets. Further analyses will include the comparison of continuous abstinence at six months between the two arms. We will also estimate reduction in tobacco use in both trial arms and compare to detect any difference. Missing data on the outcomes will not be inputted. Secondary analyses will investigate the use of, and adherence with, the various forms of therapy. Further sub-analyses will be carried out to detect differences in outcomes according to a number of variables such as gender of the participants and providers, smoking status of the provider, socio-economic status, existence of other smokers in the house or workplace and presence of children at home. We are mindful that sample size estimation was not based on these sub-analyses and therefore we may not be able to detect small differences in the outcomes according to these variables.

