#### Hypothesis

For this part of the project, we hypothesize that the 'five steps to quit' intervention (with or without offering the therapeutic option) will be more effective and cost-effective in getting people who are suspected of tuberculosis to quit nicotine use and remain quitters at both 4 weeks and six months after the treatment compared to usual care and information leaflet.

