Training of TB DOTS facilitators will also focus on the brief counselling techniques based on cognitive-behavioural model[32]. A simple desk-guide will be provided with simple algorithms and instructions for health professionals to follow "five steps to quit" programme. This will also include glossy images to support patients in understanding the benefits of stopping smoking. The TB DOTS facilitator, for all eligible patients, will be responsible for:

• Assessment of the status of their tobacco use through a checklist of questions

• Advising on benefits of quitting using visual and written educational material

• Assessment of willingness for inclusion in the study and motivation to quit using a simple scoring card

• Registration and recording of demographics and contact details

• Structured counselling using a desk guide and patient planner

• Giving a quit date after a week

On the subsequent visit in a week's time, TB DOTS facilitator will be responsible for

• assessing the status of their tobacco use

• Sharing their experience of attempting to quit, listen to the difficulties they had and providing supportive counselling to help cope with the difficulties

• Referring them to doctor if the intervention arm includes therapeutic option

• Arranging follow up in a month's time.

At follow ups at week 5 and 25, TB DOTS facilitators will be responsible for

• Reassessing status of nicotine use and recording it in the tobacco use questionnaire/register

• Reviewing treatment and other options

• Rearranging follow up as per desktop guide.

In the intervention arm 1, the primary care doctors, in addition to supervising TB DOTS facilitators, will be responsible for assessing and prescribing therapeutics (Bupropion) to patients who wish to quit and are being referred by the TB DOTS facilitators. All patients on treatment will have an additional follow up visit at week 8. In intervention arm 2, doctors will be only responsible for supervising TB DOTS facilitators. They will be provided with the appropriate training and relevant materials.

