#### The Control Arm

Participants in the control arm will also be recruited from those who are suspected of TB and screened using sputum examinations. The changes in the relevant registers will be made to record the status of nicotine use and health professionals will be given instructions on recording it on-site. The TB DOTS facilitators in control diagnostic centres will be provided with patient education leaflets to be given out to all patients recruited in the study. Apart from recording their status of nicotine use and arranging follow up at week 1 and 5, they will be provided usual care. No other components of the intervention will be delivered. We do not anticipate a significant risk of contamination, i.e. patients moving from one diagnostic centre to another, due to the geographical spread of facilities, and because no publicity will be produced regarding the availability of the treatment package in other facilities. In addition, we do not anticipate a significant benefit (other than what has been recorded previously in controls) in the control arm given that asking about nicotine use and providing information leaflets, are not, by themselves, sufficient to lead to stopping nicotine use.

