#### Outcomes

These are as follows[30]:

1. Point abstinence at 4 weeks: The proportion of trial participants who have completely given up all forms of nicotine use at four weeks after the completion of bupropion and/or brief psychological intervention

2. Continuous abstinence up to 6 months: Proportion of trial participants who remained abstinent from 4 weeks onwards up to six months

3. We will also measure tobacco use e.g. number of cigarettes smoked per day to estimate any reduction in tobacco use secondary to the intervention

4. Secondary outcomes will include incidence of various adverse affects secondary to therapy

5. Economic outcomes will be assessed in terms of healthcare cost to get one person to stop smoking at four weeks. Healthcare cost will include the treatment cost, the average duration of health professionals' time spent with the patients during assessment, advice and counselling.

6. Process outcomes will include: the proportion of tobacco users who decide to quit and registered to receive 'five steps to quit' intervention; and the proportion of people registered who continue follow-up for the full period planned

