#### Data collection

Our pilot study will determine the feasibility of our proposed tools to gather patient details and their status of nicotine use at various appointments. The modified tools will include:

1. 'Five steps to quit" intervention cards and register

2. A separate tobacco use questionnaire/register to record smoking status and motivation to quit

These approaches will allow us to record demographic details including gender, socio-economic status, presence of other smokers in the house and workplace, number of children at home, status of nicotine use, motivation level, type of therapy offered, extent to which therapy was used, adverse events and abstinence at different end points. We would adapt some of the tools already well described in the existing literature[30].

Patients who are subsequently diagnosed with TB will be followed up regularly for their TB treatment and the outcomes relevant to this study will be recorded during those visits. Trial participants who are diagnosed as not having TB and being given any of the three forms of therapy will be asked to follow up at the intervals specified. Controls not diagnosed with TB and received only usual care and a leaflet will be asked to return at 4 weeks to review their respiratory condition and to assess their status of nicotine use. Attrition is a potential problem. After piloting in phase 2, patients' mobile phone numbers will also be recorded and those who are lost to follow up will be contacted via their mobile phones to assess their status of nicotine use. A high proportion of Pakistanis possess mobile phones irrespective of socio-economic status.

Similarly, at six months in both intervention and control arms, all patients who stopped tobacco use will be contacted either via their mobile phones or landlines to assess their smoking status. According to our estimate this number will approximately be at least 264.

In order to estimate the average time spent by health professionals in delivering 'five steps to quit' intervention, our research officer will spent a day at each centre to measure and record this time.

We will also record the gender and status of nicotine use among all health professionals giving advice and include a column in the above patient record tools to record which health professional delivered which element of the package.

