### Ethical considerations

The effectiveness of specific intervention components (e.g. Bupropion) is established in trials conducted mainly in developed countries. However, the same is not true for the strategies that attempt to introduce these into existing health programmes. The proposed study is evaluating the effect of a multifaceted intervention to support patients who are suspected of TB to give up nicotine use. The research questions posed here respond to a priority need for developing countries where the existing health programmes provide an opportunity to control the increasing problem of tobacco addiction.

No participant will be deprived of any care that she would ordinarily receive. There will be no extra burden, financial or otherwise, on control subjects. Even participants in the control facilities may benefit from greater monitoring and attention. The four week follow up after their first contact is often required for their clinical condition. Upon completion of the trial, all control facilities will be offered a copy of all the training materials, training course, desk-guide and education tools. Under-powered trials are considered unethical[38]; therefore our sample size calculations are based on conservative estimates and high power.

Formal ethical approval is being granted by the Biomedical Ethics Committee of Pakistan Medical Research Council. An information sheet translated in Urdu will be given to all eligible patients. Patients will be given information on all aspects of the research project by means of verbal and written information at the inclusion. It will be clarified in the informed consent form that each patient can leave the study at any moment without having any repercussions on her usual care.

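### Point abstinence is timed from the end of treatment in the intervention arms but from the leaflet in controls, so bupropion users in arm 1 are read on a later clock

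*Protocol article*

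**What the plan says.** The Outcomes section defines point abstinence "at four weeks after the completion of bupropion and/or brief psychological intervention". Controls receive neither treatment, so the Data analysis section gives them a separate clock: the comparison is made "at 4 weeks after the completion of the treatment and in controls 4 weeks after they were given the leaflets". Continuous abstinence runs from that four-week point up to six months, and the economic outcome is the cost of one person having stopped at four weeks.

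The follow-up schedule appears in several places:

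- Table 1 gives all three arms visits at weeks 1, 5 and 25, and arm 1 an extra one at week 8. The text on delivery agrees: "All patients on treatment will have an additional follow up visit at week 8".
- The Control Arm section speaks of "arranging follow up at week 1 and 5".
- Under Data collection, controls without TB "will be asked to return at 4 weeks to review their respiratory condition and to assess their status of nicotine use". Ethical considerations counts this from first contact: "The four week follow up after their first contact is often required for their clinical condition".
- The Hypothesis expects participants to "remain quitters at both 4 weeks and six months after the treatment compared to usual care and information leaflet".

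The psychological programme takes two appointments, at first contact and week 1, with the quit date set for one week after first contact. In arm 1 the doctor prescribes bupropion to patients who wish to quit and are referred. The article does not state how long the course lasts.

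**The concern.** A comparison of quit rates is fair only if every arm is read at the same time from a common origin. Abstinence can change over the first months as some people relapse and others quit late. If one arm is read later, the contrast mixes the effect of treatment with the passage of time.

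The Outcomes definition also covers completion of either treatment or both. Within arm 1 the clock then depends on whether a patient took bupropion, which is settled after randomisation.

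Point abstinence and continuous abstinence are the two main effectiveness outcomes named in the Abstract, and the cost-effectiveness result of Objective 3 uses the four-week quitters. All three depend on this anchor. The article states the rule outright, so this is not detail left to a fuller document.

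**Working it through.** **Step 1: reading week, counted from first contact.**

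- Control: leaflet at week 0, plus 4 = week 4 (Data analysis, Data collection, Ethical considerations); or week 5 (The Control Arm, Table 1).
- Arm 2: second appointment at week 1, plus 4 = week 5. Gap to control: 0 to 1 week.
- Arm 1, bupropion users: drug ends at week E, so the reading is at week E + 4. E is not stated; I assume 5, 8 or 12.

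| Assumed E | Reading week (E + 4) | Gap to control (week 5 or 4) | Window to week 25 |
|---|---|---|---|
| 5 | 9 | 4-5 weeks | 25 − 9 = 16 weeks |
| 8 | 12 | 7-8 weeks | 25 − 12 = 13 weeks |
| 12 | 16 | 11-12 weeks | 25 − 16 = 9 weeks |

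Controls must sustain abstinence for 25 − 5 = 20 or 25 − 4 = 21 weeks. Table 1 has no visit between weeks 8 and 25. The week-8 visit meets the outcome definition only if E = 4.

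**Step 2: what the gap could do, with no true effect.** The documents give no relapse rates, so this is an illustration. Both arms follow the same curve: 20% abstinent at week 5, falling at a constant hazard to 10% or 15% at week 25.

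- Sample size section: 11 clusters of 40 = 440 per arm. Intra-cluster variation section: ICC 0.036. Design effect = 1 + 39 × 0.036 = 2.404; effective n = 440 / 2.404 = 183 per arm.
- Hazard h = ln(0.20 / p25) / 20, which is 0.0347 per week for p25 = 10% and 0.0144 for p25 = 15%.
- Arm 1 read at week w: p = 0.20 × exp(−h(w − 5)). Control read at week 5: 0.20. False difference d = p − 0.20.
- SE = √[(p(1 − p) + 0.20 × 0.80) / 183]. Two-sided rejection rate = Φ(|d|/SE − 1.96) + Φ(−|d|/SE − 1.96).

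| Curve, week 5 to 25 | Week 9 | Week 12 | Week 16 |
|---|---|---|---|
| 20% to 10% | −2.6 points, 10% | −4.3 points, 19% | −6.3 points, 37% |
| 20% to 15% | −1.1 points, 6% | −1.9 points, 8% | −2.9 points, 11% |

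Worked case, 20% to 10% at week 12: p = 0.20 × exp(−0.0347 × 7) = 0.157; d = −0.043; SE = 0.040; rejection rate 19%.

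**Step 3: partial uptake.** These figures delay everyone in arm 1. If half of arm 1 is on the bupropion clock (assumption), d halves. The range becomes about −0.6 to −3.2 points, and the same formula gives rejection rates of about 5% to 12%.

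**Step 4: direction.** Three forces act on arm 1. More time to relapse lowers its point abstinence. More time to quit raises it. A later start shortens the abstinence that must be sustained, which favours arm 1 on the continuous outcome. The first two can cancel. If half of early quitters stay abstinent over 20 weeks, 8 weeks' delay turns 20% into 20% × 0.5^(8/20) = 15.2%; adding 5 points of late quitters brings it back to 20.2%.

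**The case against.** The strongest reply is that the trial can still produce comparable readings. Table 1 brings every arm back at weeks 5 and 25, and arm 2 and control are read within a week of each other. That stands, and it limits the point to bupropion users in arm 1. It does not remove the point, because neither the outcome definition nor the analysis text uses week 5 as the common reading.

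A second reply is that a post-treatment outcome is a deliberate choice, since abstinence on the drug may not last. That is a fair reason to report the figure for arm 1, but not to set it against controls read weeks earlier.

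A reader might infer more than the documents support:

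- **That quit rates are not comparable in any arm.** Arm 2 against control is essentially unaffected.
- **That the planned power collapses**, by letting the 20% quit rate decay over a late reading. The Quit rates section sets 20% against 10% as six-month rates, and the article gives no early rates to decay from.
- **That the bias has a known sign.** Step 4 shows it does not.
- **That the six-month reading is taken at different times.** The week-25 visit is common to all arms, and Data collection adds telephone contact at six months for those who stopped, in intervention and control arms alike. What differs is where the window starts, and so who counts as having stopped.
- **That the control schedule is given in three conflicting ways.** The four-week return concerns controls without TB, and naming weeks 1 and 5 does not exclude week 25. What remains is week 4 against week 5.

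**Conclusion.** The point holds for arm 1. As written, bupropion users are read about 4 to 12 weeks later than controls if the drug ends between weeks 5 and 12 (assumed). Their continuous-abstinence window is then 9 to 16 weeks, against 20 to 21 in controls. The clock within arm 1 depends on treatment taken after randomisation, and the cost per quitter at four weeks inherits the same mismatch.

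The unequal anchors are certain, because the text states them. Size and direction are not. The false differences of about 1 to 6 points and rejection rates of about 6-37% rest on an assumed course length, assumed relapse curves, no late quitting and the delay applying to all of arm 1; partial uptake shrinks them. They show that the effect could matter, not what it would be. The fault is best corrected before data are collected, because a bias of unknown sign is hard to undo if arm-1 status is recorded only on its own clock.

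**What to change.** For the between-arm comparison, define point abstinence and the start of continuous abstinence from one common anchor in all three arms. First contact is the simplest. A quit date would also serve if it were set the same way in each arm, which would need a nominal date for controls because they are given none. Point abstinence would then be read at week 5 and continuous abstinence would run from week 5 to week 25. Table 1 already schedules both visits for every arm, and they fall 4 and 24 weeks after a quit date at week 1. Use the same week-5 reading for the cost per quitter.

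Keep abstinence four weeks after bupropion as a descriptive figure for arm 1. Reconcile the outcome timing in Hypothesis, Outcomes, The Control Arm, Data collection and Data analysis with Table 1, including the week-4 and week-5 control follow-up and the six months counted from treatment. When the controls' clinical review takes place is for the investigators to settle.

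The cost is protocol wording; no sample-size figure changes and no visit is added. One downside should be stated: some arm-1 patients may still be on treatment at week 5, which affects both the point-abstinence reading and the start of the continuous window.

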#### Sample size

We have estimated a sample size of 33 clusters (diagnostic centres) 11 in each arm of the trial. Each cluster size will be 40. The actual number of patients recruited in each cluster will be 50 patients with suspected tuberculosis each [assuming 80% will complete the trial up to the review at 6 months as per study in Sudan[24]] to give 80% power to detect a difference in quit rates of 20% in the intervention arm compared with 10% in the control arm. The value of α is set at 0.05. The assumptions underlying this estimation are:

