##### Quit rates

We base our cessation rates on the cumulative estimates in the recent systematic reviews conducted by Cochrane Tobacco Addiction Group [33-36]. According to these reviews, brief advice by physicians, nicotine replacement therapy (NRT), and use of bupropion can improve 6 month smoking quit rates to 74%, 77% and 94% respectively. All three approaches are part of our "5-steps to quit" intervention and it is reasonable to expect an effect size of at least 94% in our study. We would recruit our patients from a group who are suspected of tuberculosis with respiratory symptoms. It is likely that the quit rates may even be higher than the above in both treatment arms. The trial of treating tobacco addiction in TB patients in Sudan showed a sustained abstinence of 66% in the intervention group[24]. We also expect some loss of effectiveness due to the fact that this is not an efficacy trial and treatment will be provided integrated within an existing programme. However, we assume that this loss in effectiveness with the intervention strategy applied to routine practice will be off-set by higher quit rates in patients with respiratory symptoms suspected of tuberculosis. For the purpose of this study, we assume that the quit rates at 6 months would be at least 20% in the intervention group versus 10% in the control group.

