##### Attrition Rates

The sample size calculation incorporates an attrition rate of 20%. This is based on the observations made in the trial of tobacco control in TB patients in Sudan where less than 20% patients defaulted over a period of six months. An intention to treat analysis will account for any non-differential loss to follow up. As part of DOTS, patients with diagnosed TB are generally followed up for a period of six months. However, follow up of non-TB patients will be arranged as part of the trial.

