##### Intra-cluster variation

The intraclass cluster coefficient (ICC) of the outcomes is an important factor in estimation of the sample size for a cluster RCT. It is generally estimated from the previous studies of smoking prevalence and its outcomes in similar settings. However, we found very few studies reporting ICC in similar settings. We use an ICC of 0.036 which has been used estimated from trials conducted in primary care clusters in the UK[37].

### Objective 4

To determine barriers and drivers to the provision of treatment of tobacco dependence within TB programmes (qualitative component of Phase III)

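### The stated 80% power does not follow from the protocol's own inputs: 11 clusters of 40 per arm at ICC 0.036 give about 77%

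*Protocol article*

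**What the plan says.** All inputs are in the protocol article, under Objective 3.

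- Clusters (Sample size): "We have estimated a sample size of 33 clusters (diagnostic centres) 11 in each arm of the trial".
- Analysed size (Sample size): "Each cluster size will be 40". Recruitment is 50 per centre, on the assumption that 80% complete to six months.
- Error rate (Sample size): "The value of α is set at 0.05". Sidedness is not given.
- Target (Sample size): "to give 80% power to detect a difference in quit rates of 20% in the intervention arm compared with 10% in the control arm".
- Effect (Quit rates): "we assume that the quit rates at 6 months would be at least 20% in the intervention group versus 10% in the control group".
- Attrition (Attrition Rates): "The sample size calculation incorporates an attrition rate of 20" per cent.
- Clustering (Intra-cluster variation): "We use an ICC of 0.036".
- Missing outcomes (Data analysis): not to be imputed, so the analysed cluster is the completers.

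Ethical considerations, after noting that under-powered trials are considered unethical, adds that "our sample size calculations are based on conservative estimates and high power".

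**The concern.** A cluster trial's power follows directly from the number of clusters, the analysed cluster size, the ICC and the two proportions. All of these are stated here, so the 80% can be checked without any outside figure. It does not come out at the stated analysed size of 40, but it does at the recruited size of 50. Either the power or the number of clusters is therefore inconsistent with the attrition assumption.

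What is at stake is the accuracy of the power statement for the intervention-versus-control comparison, and of the ethics statement that relies on it. The design itself is not invalidated.

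**Working it through.** **Inputs.** p1 = 0.20, p2 = 0.10, k = 11 clusters per arm, m = 40 analysed (50 × 0.8) or 50 recruited, ICC = 0.036, alpha = 0.05 taken as two-sided (z = 1.960), 80% power (z = 0.8416).

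**Step 1: sample size under individual randomisation.** With p̄ = 0.15,

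n = [1.960 × √(2 × 0.15 × 0.85) + 0.8416 × √(0.16 + 0.09)]² / 0.10² = 198.96, so 199 per arm.

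The unpooled formula gives 196.2.

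**Step 2: reproduce the plan's figure.** At m = 50 the design effect is 1 + 49 × 0.036 = 2.764.

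- Clusters needed: 198.96 × 2.764 / 50 = 10.999, so 11.
- Effective n per arm: 550 / 2.764 = 198.99. Power is 80.0% (pooled).

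Both stated figures, 11 clusters and 80%, appear here.

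**Step 3: the same calculation at the stated cluster size.** At m = 40 the design effect is 1 + 39 × 0.036 = 2.404.

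- Clusters needed: 198.96 × 2.404 / 40 = 11.96 (pooled) or 196.22 × 2.404 / 40 = 11.79 (unpooled). Both round up to 12.
- Analysed patients needed per arm: 198.96 × 2.404 = 478 (pooled) or 472 (unpooled), against 11 × 40 = 440 planned.
- Effective n per arm: 440 / 2.404 = 183.0.
- Pooled power: null SE = √(0.255 / 183.0) = 0.03733; alternative SE = √(0.25 / 183.0) = 0.03696; Φ[(0.10 − 1.960 × 0.03733) / 0.03696] = Φ(0.726) = 76.6%.
- Unpooled power: Φ(0.10 / 0.03696 − 1.960) = Φ(0.746) = 77.2%.

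**Step 4: what 11 × 40 does deliver.** With 10% in control, 80% power is reached at an intervention rate of 20.5% (pooled) or 20.4% (unpooled). Twelve clusters of 40 per arm give 80.1% for 20% v 10%.

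**Step 5: other methods and readings.**

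| Calculation | 11 × 40 | 11 × 50 |
|---|---|---|
| Pooled z, two-sided | 76.6% | 80.0% |
| Unpooled z, two-sided | 77.2% | 80.5% |
| Arcsine, two-sided | 77.5% | 80.8% |
| Noncentral t, 20 df | 73.0% | 76.5% |
| One-sided 0.05, pooled z | 85.2% | 87.7% |
| Both intervention arms combined v control | 86.7% | 89.5% |

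No two-sided pairwise method gives 80% at 11 × 40. On the t calculation, 80% at 11 × 40 applies to about 21% v 10%, and 13 clusters of 40 per arm would be needed for 20% v 10% (80.6%; 12 give 77.1%).

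**The case against.** **The miss is small.** This stands. By the normal approximation it is 2.8 to 3.4 points, or one cluster per arm, and it disappears if the intervention rate is 20.5% rather than 20%. An ICC of about 0.031 would also restore 80%, and the protocol admits it found very few ICCs from similar settings. But 0.036 is the value it chose, and 11.96 clusters does not round to 11.

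**Attrition may be lower.** Attrition Rates reports that fewer than 20% defaulted in the Sudan study, and Data collection adds telephone tracing. With 45 analysed per cluster, power is 78.5% to 79.1%, which is closer but still short. The stated calculation uses 40.

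**Another test or comparison may have been meant.** Sidedness is not stated, and the hypothesis covers the intervention with or without the therapeutic option. A one-sided test gives 85.2% and combining the intervention arms gives 86.7%. Neither reproduces 80%, and the Sample size wording, one intervention arm against control with 11 centres each, points to a pairwise comparison.

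**Stronger readings that the documents do not support.**

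- A reader might conclude that power is 73%. That figure needs a cluster-level t-test on 20 degrees of freedom, which the protocol does not specify, so it belongs in a side note.
- A reader might say that 11 clusters would be enough if nobody were lost. That holds only by the normal approximation; by t, 11 × 50 gives 76.5%.
- A reader might say that attrition was ignored. Recruitment was raised from 40 to 50 for it, so the Attrition Rates sentence is true of the recruitment target. The estimate of at least 264 quitters under Data collection equals 20% of 33 × 40, which is consistent with 40 completers per centre in that part of the planning. That the cluster count was worked out at 50 is an inference from the numerical match.
- A reader might want the word conservative withdrawn from the ethics paragraph. It concerns the assumed inputs, which this point does not challenge.

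**Conclusion.** The point holds as an arithmetic inconsistency. On the protocol's stated inputs, 11 clusters of 40 per arm give about 77% power for 20% v 10%, not 80%, and 12 clusters per arm are needed. This rests on a two-sided alpha of 0.05, a pairwise comparison of one intervention arm with control, equal cluster sizes and the usual design effect. The shortfall is modest: about 3 points by the normal approximation, and about 7 if the analysis were a cluster-level t-test on 20 degrees of freedom. The probable cause, a cluster count worked out at the recruited size of 50, is suggested by the exact match but not stated. The correction affects a reported figure, not the validity of the design.

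**What to change.** 1. **Sample size.** State that alpha is two-sided, if that is meant, and restate the power: 11 clusters per arm with 40 analysed per cluster and ICC 0.036 give about 77% power for 20% v 10% (normal approximation), and 80% power applies to about 20.5% v 10%. Add a note that a cluster-level t-test on 20 degrees of freedom would give about 73%, with 80% power at about 21% v 10%.
2. **Attrition Rates.** Keep the sentence, but say that the 20% was used to raise recruitment from 40 to 50 per centre, and show the calculation with 40 analysed.
3. **Ethical considerations.** Replace the reference to high power with the corrected figure.

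The cost is text only. No patients or centres are added and the analysis does not change; the stated power becomes slightly less favourable. Keeping the 80% claim instead would take 12 centres per arm by the normal approximation: 3 more centres and, at 50 each, 150 more recruits.
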